#### 4.7.4. Clinical Outcome Variables and Assessment

The primary outcome is the change in STAI-S score from baseline to immediately after intervention. Secondary outcomes include postoperative pain intensity assessed using the Visual Analogue Scale (VAS), postoperative analgesic use, patient satisfaction, and VR-related adverse effects. These outcomes will be measured preoperatively on the day before surgery, before the VR content exposure, and after. Measurements will be made again postoperatively—within 24 h. Preoperative and postoperative STAI-S and VAS will be compared for data analysis.

The baseline assessment is conducted one day before surgery, prior to the VR intervention, to capture the patient’s preoperative state under conditions closest to the actual surgical context. We believe this timing best reflects the anxiety and pain levels that the VR intervention aims to reduce. The postoperative assessment within 24 h is intended to evaluate the immediate effect of the intervention on perioperative anxiety and pain, which is the primary focus of our study. We acknowledge that longer-term outcomes may differ, but these are beyond the scope of the current trial, which specifically targets the short-term perioperative period (see Table 2).

The secondary outcome will be the patients’ quality of life and satisfaction (EVAN-G) of the VR intervention, time spent thinking about pain assessed, and postoperative analgesics measured from patient treatment charts within 24 and 48 h postoperatively and used for data analysis, as the level of satisfaction and thinking time spent on pain can contribute to an increased perception of pain.

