## 3. Objectives

The aim of this research study is to evaluate the impact of immersive VR exposure on preoperative anxiety and pain, and, additionally, to assess whether VR intervention would significantly alleviate pain and anxiety levels of patients undergoing complex spinal surgeries. We hypothesize that the application of preoperative VR-based intervention will alleviate anxiety and pain both pre- and postoperatively when it is used as treatment to complement standard care compared to standard routine care alone, and that it may lead to better outcomes and higher satisfaction in patients. The primary objective is to evaluate whether procedural/educational VR reduces preoperative anxiety compared with standard care. Secondary objectives include comparing relaxation/distraction VR versus standard care, and procedural/educational VR versus relaxation/distraction VR with respect to postoperative pain, analgesic use, and patient satisfaction.

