#### 4.7.3. Standard Care (Control) Group

In the standard group, patients will only receive standard care and be provided with routine descriptions of the preoperative experience, where a surgeon will explain to them what the preoperative experience will entail.

After VR intervention, psychometric assessments of anxiety, pain score, and satisfaction will be performed and evaluated shortly before the intended surgery. Subsequently, the patients will undergo their planned surgical procedure. Postoperative data on analgesic use and pain will also be collected in the recovery area.

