### 4.8. Data Collection

#### Baseline Value Measurement

On the day before surgery, after informed consent is obtained, evaluations, which include sociodemographic data and the psychometric questionnaires (STAI-S, PSS-10, BDI-II), pain score (VAS), and satisfaction (EVAN-G), will be collected by the researcher before the VR experience (see Table 3).

Perioperative anesthesia and analgesia management will follow standardized institutional protocols whenever feasible. Variables including anesthetic technique, intraoperative opioid administration, postoperative opioid consumption, rescue analgesic use, surgery duration, and perioperative complications will be prospectively recorded and considered in adjusted secondary analyses.

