### 4.9. Statistical Analysis

The statistical analysis will be performed under the mentorship of a biostatistician experienced in neurosurgical research. The nominal data will be presented as *n* (% of the total). The dependencies between them will be assessed using the test chosen based on the size of the smallest sample. All analyses will follow an intention-to-treat approach. The primary endpoint (change in STAI-S score from baseline to immediately postintervention) will be analyzed using one-way ANCOVA adjusted for baseline STAI-S. Pairwise comparisons will be Bonferroni-corrected. Secondary outcomes will be analyzed as follows: VAS pain at 24 h (ANCOVA adjusted for opioid dose), total opioid consumption (ANOVA or Kruskal–Wallis depending on distribution), patient satisfaction (Kruskal–Wallis), and rescue analgesic use (χ^2^ test). Longitudinal measures (baseline → post-VR → postoperative) will be evaluated with a linear mixed-effects model including group, time, and group × time interaction. Normality will be tested using the Shapiro–Wilk test. Missing data will be assessed for pattern and mechanism. Multiple imputation (m = 10) will be used if appropriate. Longitudinal analyses will primarily rely on linear mixed-effects models, which are robust to missing observations under missing-at-random assumptions. The primary comparison will evaluate procedural/educational VR versus standard care with respect to STAI-S score change. Secondary comparisons will include relaxation/distraction VR versus standard care and procedural/educational VR versus relaxation/distraction VR. Postoperative pain analyses will additionally be adjusted for perioperative opioid consumption and surgery duration when appropriate. Statistical analysis will be performed using STATISTICA 13.1 (TIBCO, Palo Alto, Santa Clara, CA, USA) and two-sided α = 0.05.

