## Figures and Tables

**Table 1 brainsci-16-00587-t001:** Eligibility Criteria for Study Enrollment.

Inclusion Criteria	Exclusion Criteria
Adult patients between 18–70 years old Patient’s admission prior to surgery day (at least 1 day) Patients’ first surgery with no prior surgical history cervical vs. lumbar vs. thoracic) Type of spine surgery (e.g., cervical vs. lumbar vs. thoracic) Surgical approach (e.g., minimally invasive vs. open) Anesthetic technique (e.g., general) Expected hospital stay—2 days Capable of providing informed consent and participate in the study follow-up questionnaire Patients speak English	Congestive heart failure, hypertension and anti-hypertensive medications Adrenal insufficiency Cognitive impairment (evaluated by MMSE, MoCA) Cerebrovascular diseases, ophthalmological diseases (strabismus, diplopia, retina degeneration, glaucoma), neurological conditions (epilepsy or seizure, dementia, vertigo, dizziness, motion sickness)—evaluated by: history taking, examination, vision test (Ishihara test) Auditory impairment Psychiatric illness (schizophrenia, bipolar disorder, psychotic depression)—(evaluated by MINI questionnaire) Patients with neuropathic pain Use of sedative drugs, anti-depressants, anxiolytics, and anti-epileptic drugs Claustrophobia GCS < 15

**Legend:** MMSE, Mini-Mental State Examination; MoCA, Montreal Cognitive Assessment; MINI, The Mini International Neuropsychiatric Interview; GCS, Glasgow Coma Scale.

**Table 2 brainsci-16-00587-t002:** Primary and secondary outcome assessment.

Timepoint	Assessment	Measures
Day before surgery (pre-VR)	Baseline	STAI-S, VAS pain
Day before surgery (post-VR)	Immediately after VR intervention	STAI-S, VAS pain, patient experience satisfaction
Within 24 h after surgery	Postoperative	VAS pain, analgesic use

**Table 3 brainsci-16-00587-t003:** Preoperative and postoperative psychometric scales.

Baseline Values
Patients’ demographics: age, sex, education, medical history (comorbidities), medication, surgery type, duration, ASA status Anxiety (STAI-S) Stress (PSS-10) Depression (BDI-II) Pain score (VAS) Satisfaction (EVAN-G) Cognitive (ACE-III) Personality test (PID-5) Postoperative analgesia (Medical charts and records)

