**Legend:** ASA, American Society of Anesthesiologists; STAI-S: State-Trait Anxiety Inventory Scale; PSS-10, Perceived Stress Scale; BDI-II, Beck Depression Inventory; VAS, Visual Analogue Scale; EVAN-G, Evaluation du Vecu de l’Anesthesie Generale; ACE-III, Addenbrooke’s Cognitive Examination; PID-5, Personality Inventory for DSM-5.

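### Satisfaction is worded as satisfaction with the VR intervention but compared with an arm that gets no VR, so its object, instrument and time point need reconciling

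*Protocol article*

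**What the plan says.** Section 4.7.4 of the protocol article describes satisfaction twice. Its first paragraph lists it in general terms among the secondary outcomes: "postoperative analgesic use, patient satisfaction, and VR-related adverse effects". That paragraph goes on to say that the outcomes are measured the day before surgery, before and after VR exposure, and again within 24 h after the operation. Its last paragraph names an instrument and an object: "The secondary outcome will be the patients’ quality of life and satisfaction (EVAN-G) of the VR intervention".

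On who is compared, Section 3 states: "Secondary objectives include comparing relaxation/distraction VR versus standard care, and procedural/educational VR versus relaxation/distraction VR with respect to postoperative pain, analgesic use, and patient satisfaction". Section 4.9 gives the test as "patient satisfaction (Kruskal–Wallis"), without limiting it to the two VR arms. On what controls receive, Section 4.7.3 says: "In the standard group, patients will only receive standard care".

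On instrument and timing, the legend under Table 3 reads "EVAN-G, Evaluation du Vecu de l’Anesthesie Generale". Section 4.8 has "satisfaction (EVAN-G), will be collected by the researcher before the VR experience". In Table 2, satisfaction appears in one row only, immediately after VR on the day before surgery: "STAI-S, VAS pain, patient experience satisfaction". The postoperative row of that table has VAS pain and analgesic use, and no satisfaction measure.

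**The concern.** A between-arm comparison of a rating needs every arm to rate the same thing. Section 4.7.4 makes the VR session the thing rated, and one of the three arms has no VR session. The stated object of the endpoint therefore contradicts the comparison that Sections 3 and 4.9 plan with it.

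What is at stake is how a secondary result can be read. If VR patients rate their headset session while controls rate routine preparation, a difference in ranks mixes any effect of VR on satisfaction with the difference between two questions, and no analysis can separate them afterwards. Section 4.4 acknowledges that participants cannot be fully blinded to VR exposure, so a subjective item that names VR as its object deserves particular care.

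**Working it through.** **Arm sizes.** Section 4.3.1 gives 42 per arm and 15% attrition: 42 / (1 − 0.15) = 49.4, rounded up to 50, and 3 × 50 = 150. This reproduces the stated enrolment.

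**Comparisons affected.** Three arms give 3 × 2 / 2 = 3 pairs:

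- procedural/educational VR versus relaxation/distraction VR: both arms have a VR session to rate;
- procedural/educational VR versus standard care: one arm has none;
- relaxation/distraction VR versus standard care: one arm has none.

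So 2 of 3 pairs involve standard care. Section 3 ties satisfaction explicitly to two pairs only (the first and third above), and 1 of those 2 involves standard care.

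Section 4.9 does not say in words that the Kruskal–Wallis test covers three groups. That is an inference from a three-arm design and a multi-group test. The conflict does not depend on it, because the objective in Section 3 needs control data in any case.

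**The possible readings of the endpoint, side by side.**

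| Reading | Who shares a common object | Comparisons that ask the same question |
|---|---|---|
| Satisfaction with VR (literal wording, Section 4.7.4) | two VR arms, 2 × 50 = 100 enrolled | 1 of 3 |
| EVAN-G as the legend names it, after surgery | all arms, 150 enrolled | 3 of 3 |
| EVAN-G at the only satisfaction row in Table 2 | no arm has yet had anaesthesia for this operation | the object is undefined in every arm |

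The first row loses the comparisons with standard care. The second preserves all of them, but Table 2 does not schedule it. The third is what Table 2 schedules, and there the named instrument asks about something that has not yet happened.

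**Timing.** Section 4.7.4, first paragraph, implies satisfaction within 24 h after surgery. Table 2 omits it there. Section 4.7.3 places it after VR and shortly before surgery. Section 4.8 also collects it before VR. A reader cannot tell which of these values enters the Kruskal–Wallis test.

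**The case against.** The strongest reply is that EVAN-G is not a VR scale. The legend spells it out as an evaluation of the general-anaesthesia experience, Section 4.8 collects it before any VR, and Sections 3 and 4.9 and the first paragraph of 4.7.4 speak simply of patient satisfaction. On this view the reference to VR is one loose phrase in a condensed article.

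Much of that stands. A reader might infer that the 50 standard-care patients cannot be scored and that the comparisons with them are lost. The documents do not support this, because controls can complete the named questionnaire. Nor does the row label in Table 2 exclude them: the same row carries STAI-S and VAS pain, which controls must also supply, and Section 4.5 describes an immediate assessment after either VR or standard care. A reader might also fear that controls would be scored at the bottom of the scale, which would guarantee a difference. Nothing in the article suggests such a rule.

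What does not stand is that the wording is therefore harmless. If EVAN-G measures the anaesthesia experience, the object stated in Section 4.7.4 is wrong. If it is meant to capture VR, the comparison with standard care is wrong. The rescue through EVAN-G also needs a postoperative administration that Table 2 does not show. What an endpoint measures, and in whom, is protocol content and not a detail left to an analysis plan. Here it is stated inconsistently, not merely left out.

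**Conclusion.** The point holds as an inconsistency in the definition of one secondary endpoint. The object in Section 4.7.4 conflicts with the planned comparison with standard care, and the instrument and the Table 2 time point do not resolve the conflict. Read literally, it affects 2 of the 3 pairwise comparisons, or 1 of the 2 satisfaction comparisons named in Section 3. If the endpoint is EVAN-G given postoperatively in all arms, it affects none.

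No numerical bias is claimed: the article gives no distribution for satisfaction scores from which one could be derived. The primary endpoint, sample size and randomisation are untouched. The conclusion rests on reading the instrument as the legend names it, and on patients having had general anaesthesia by the postoperative assessment; Table 1 gives general anaesthesia as an example of technique. The change should be made because the wording bears on a stated objective and is almost free to correct.

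**What to change.** 1. In Section 4.7.4, drop the closing words of the definition that tie the rating to VR. Define the compared endpoint as EVAN-G patient satisfaction, with the same items, the same object and the same time point in all three arms.
2. In Table 2, list this endpoint at the postoperative assessment within 24 h. That agrees with the first paragraph of Section 4.7.4 and is when all arms have had the experience the instrument names. Bring the satisfaction timing in Sections 4.7.3 and 4.8 into line, and say which value enters the test in Section 4.9.
3. If a rating of the VR session is wanted, give it its own name and report it for the two VR arms only, descriptively or as a two-group comparison.

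Relabelling the endpoint as satisfaction with perioperative care while leaving it at the present Table 2 time point would not work, because that care cannot be rated the day before surgery. Object, instrument and time point have to be changed together.

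The cost is wording in Section 4.7.4, one move in Table 2 and the matching timing statements. No new instrument is needed and no sample size changes. If EVAN-G is not already given after surgery, one administration is added at a visit that already exists. The small downside is that the compared endpoint no longer measures liking of VR itself, which moves to the separate result for the VR arms.

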### 4.8. Data Collection

#### Baseline Value Measurement

On the day before surgery, after informed consent is obtained, evaluations, which include sociodemographic data and the psychometric questionnaires (STAI-S, PSS-10, BDI-II), pain score (VAS), and satisfaction (EVAN-G), will be collected by the researcher before the VR experience (see Table 3).

Perioperative anesthesia and analgesia management will follow standardized institutional protocols whenever feasible. Variables including anesthetic technique, intraoperative opioid administration, postoperative opioid consumption, rescue analgesic use, surgery duration, and perioperative complications will be prospectively recorded and considered in adjusted secondary analyses.

### 4.9. Statistical Analysis

The statistical analysis will be performed under the mentorship of a biostatistician experienced in neurosurgical research. The nominal data will be presented as *n* (% of the total). The dependencies between them will be assessed using the test chosen based on the size of the smallest sample. All analyses will follow an intention-to-treat approach. The primary endpoint (change in STAI-S score from baseline to immediately postintervention) will be analyzed using one-way ANCOVA adjusted for baseline STAI-S. Pairwise comparisons will be Bonferroni-corrected. Secondary outcomes will be analyzed as follows: VAS pain at 24 h (ANCOVA adjusted for opioid dose), total opioid consumption (ANOVA or Kruskal–Wallis depending on distribution), patient satisfaction (Kruskal–Wallis), and rescue analgesic use (χ^2^ test). Longitudinal measures (baseline → post-VR → postoperative) will be evaluated with a linear mixed-effects model including group, time, and group × time interaction. Normality will be tested using the Shapiro–Wilk test. Missing data will be assessed for pattern and mechanism. Multiple imputation (m = 10) will be used if appropriate. Longitudinal analyses will primarily rely on linear mixed-effects models, which are robust to missing observations under missing-at-random assumptions. The primary comparison will evaluate procedural/educational VR versus standard care with respect to STAI-S score change. Secondary comparisons will include relaxation/distraction VR versus standard care and procedural/educational VR versus relaxation/distraction VR. Postoperative pain analyses will additionally be adjusted for perioperative opioid consumption and surgery duration when appropriate. Statistical analysis will be performed using STATISTICA 13.1 (TIBCO, Palo Alto, Santa Clara, CA, USA) and two-sided α = 0.05.

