## Abstract

**Background**: Preoperative anxiety and postoperative pain are prevalent and are frequently associated with poor postoperative functional outcomes. Comprehensive postoperative management, including both pharmacological and psychological components, is essential for proper postoperative care and better recovery. While the analgesic effect of traditional non-pharmacological intervention, such as cognitive behavior therapy, has been investigated by other trial studies, the newer innovative methods for delivering psychological interventions for reducing anxiety and pain are extensively being investigated. Virtual reality (VR) has emerged as a novel and promising technology that offers opportunities to mitigate patient perception and cognitive responses, and has been shown to be associated with lower levels of anxiety and pain. The aim of this randomized clinical trial (RCT) is to determine whether delivering the psychological content through virtual reality (VR) along with the standard preoperative and postoperative care results in better anxiety and pain relief outcomes than standard care in patients undergoing spinal surgery. **Methods**: This study protocol outlines a parallel-group RCT to be conducted in the Department of Neurosurgery at the University Clinical Hospital of Medical University of Lodz. The objective is to assess the efficacy of immersive VR environments in reducing preoperative anxiety and postoperative pain intensity in the following day after surgery. Adult patients (18–70) will be randomly assigned to either (1) standard care before surgery (control group), (2) VR exposure simulating the hospital environment alongside standard care, or (3) VR-based exposure to calming natural landscapes accompanied by soothing background sound along with standard care. In each group, a minimum of 50 patients will be recruited. The primary outcome is the change in preoperative anxiety measured using the State-Trait Anxiety Inventory-State (STAI-S) scale from baseline to immediately after intervention. Secondary outcomes include postoperative pain measured using the Visual Analogue Scale (VAS), postoperative analgesic consumption, patient satisfaction, and VR-related adverse effects. To facilitate a comprehensive understanding of the VR intervention’s impact, the primary outcome will be complemented with measures of the adverse effects, level of immersion, and level of presence in the VR environment. Secondary outcomes of self-reported satisfaction scores and postoperative analgesics from patients’ medical charts will be assessed. **Conclusions**: This trial will evaluate whether VR-based interventions may reduce preoperative anxiety and postoperative pain in patients undergoing spine surgery. This study may provide evidence supporting the future implementation of VR as a non-pharmacological adjunct in perioperative care. This intervention may hold significant clinical relevance clinically, particularly in patients with high level of preoperative anxiety, by offering an alternative method to pharmacological anxiolytics in the future.

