### 4.5. Instruments and VR Utilization

The study affects all three groups, and the VR intervention includes only one session. All intervention sessions will be carried out individually. After these assessments, the patients will be oriented to the VR goggles and headset and given tutorials and instructions on how to use the device and how to remove it when they encounter potentially unwanted side effects such as dizziness, headache, nausea, or vomiting. In such cases, the procedure will be stopped and considered a withdrawal.

On the day before surgery, following baseline assessment and informed consent, the researcher will randomly allocate the patients to the VR group, control group, and VR relaxation/distraction group.

The study timeline will proceed as follows: enrollment and informed consent → baseline psychometric and pain assessments → randomization → VR or standard-care intervention on the day before surgery → immediate postintervention assessment → surgery → postoperative assessment within 24 h and analgesic assessment within 24–48 h postoperatively.

VR-related adverse effects, including dizziness, nausea, headache, cybersickness, and visual discomfort, will be prospectively recorded and analyzed descriptively throughout the intervention period.

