#### 4.7.2. VR Relaxation/Distraction Intervention Group Patients

The VR relaxation/distraction intervention group will be provided with standard routine care followed by a VR intervention designed to facilitate relaxation and distraction. This intervention utilizes numerous highly immersive environments, each stimulating a distinct natural setting (i.e., natural landscapes, urban parks, tropical beaches and forests) with background music, delivered via a commercially available application (i.e., Nature Treks VR (Greensky Games, London, UK), accessed via the Meta Quest platform (Meta Platforms, Inc., Menlo Park, CA, USA)) through a head-mounted display (HMD) and headsets. Patients can navigate these environments using a handheld controller, engaging in context-specific activities such as walking along a beach or climbing a mountain. These interactions are accompanied by dynamic environmental changes, which enhance the sense of presence, facilitate immersive engagement, and contribute a vivid experience.

These interventions will be delivered and preoperative assessment will take place on the day before surgery or at the moment the patient is recruited. Additionally, the postoperative assessment will be conducted within 24 h after the operation. The rationale for comparing both interventions is to explore whether cognitive (information-based) or emotional (relaxation-based) mechanisms provide greater benefit in the perioperative context.

We aimed at assessing the value of educational and exposure to stress factors in comparison to the second (2nd) intervention, where we use various relaxing immersive and game-based destinations that patients have access to prior to their respective surgeries.

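### Section 4.9 analyses pain at 24 h, but the schedule collects one postoperative VAS at any time up to 24 h and adds an unplaced recovery-area score

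*Protocol article*

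**What the plan says.** The protocol article times postoperative pain in several places:

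- **Abstract:** "postoperative pain intensity in the following day after surgery".
- **Section 4.5 (timeline):** "postoperative assessment within 24 h and analgesic assessment within 24–48 h postoperatively".
- **Section 4.7.2:** "the postoperative assessment will be conducted within 24 h after the operation".
- **Section 4.7.3:** "Postoperative data on analgesic use and pain will also be collected in the recovery area".
- **Section 4.7.4:** "Measurements will be made again postoperatively—within 24 h", with the purpose given as "The postoperative assessment within 24 h is intended to evaluate the immediate effect of the intervention on perioperative anxiety and pain".
- **Table 2:** a single postoperative row, headed "Within 24 h after surgery", which holds VAS pain and analgesic use.
- **Section 4.9 (analysis):** "VAS pain at 24 h (ANCOVA adjusted for opioid dose".

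The mixed model in section 4.9 has three time levels, and only one of them is postoperative. The covariates named for pain are opioid dose or consumption and surgery duration.

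**The concern.** The analysis names a fixed time point that the schedule does not collect. A limit of 24 h admits a score taken one hour after surgery as readily as one taken the next morning. The recovery-area score in section 4.7.3 meets that limit, so staff who follow Table 2 could validly enter it in the single postoperative row. It would then be analysed as pain at 24 h. Another patient's entry could come from the following day.

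If pain changes over the first day, part of the variation in the analysed score reflects when it was taken and not how the patient fared. That dilutes the comparison of arms, and a published 24 h result would not describe pain at 24 h. Pain is the first-listed secondary outcome (abstract and section 4.7.4) and part of the hypothesis in section 3. A later analysis plan cannot repair this, because no analysis rule can recover a score that was not taken at a common time.

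**Working it through.** **Step 1: compare the passages.**

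| Place | Timing of postoperative pain | What it fixes |
|---|---|---|
| Abstract | day after surgery | a calendar day, no hour |
| Sections 4.5, 4.7.2, 4.7.4; Table 2 | up to 24 h | upper limit only |
| Section 4.7.3 | recovery area | a place, soon after surgery |
| Section 4.9, pain ANCOVA | 24 h | a point in time |
| Section 4.9, mixed model | one postoperative level | no second score |

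The abstract and the 24 h limit are compatible, since a next-day visit made before 24 h have passed satisfies both. Two mismatches remain. The analysed point is not the scheduled window, and the recovery-area score has no slot of its own. No passage says which score is analysed if there are two, and none lists time since surgery as a covariate or a recorded variable.

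**Step 2: illustrate the size.** The protocol has no figure to reproduce, because it gives no VAS mean, SD, effect or power. All inputs here are assumptions: a 0–10 scale, between-patient SD 2, mean pain falling linearly by F = 1, 2 or 3 points between 1 h and 24 h, and scores spread evenly over those 23 h.

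- SD added by timing = F/√12.
- Rise in variance = (F²/12)/2².
- Loss of effective sample = 1 − 1/(1 + rise).
- Shift in the contrast if mean collection times differ by 4 h = 4F/23.

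| F | Added SD | Rise in variance | Loss of effective sample | Shift for 4 h |
|---|---|---|---|---|
| 1 | 0.29 | 0.083/4 = 2.1% | 2.0% | 0.17 |
| 2 | 0.58 | 0.333/4 = 8.3% | 7.7% | 0.35 |
| 3 | 0.87 | 0.750/4 = 18.8% | 15.8% | 0.52 |

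**Step 3: express it as power.** Take the same SD and falls on a 100 mm scale (SD 20 mm; falls of 10, 20 and 30 mm), an assumed true difference of 10 mm, 50 per arm and two-sided α = 0.05. Power is 0.71 without timing noise. It becomes 0.70, 0.67 and 0.63 with it.

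**Step 4: see what a narrower window does.** If all scores fall within 8 h on the same line, the added SD is (8F/23)/√12. That is 0.10 for F = 1 and 0.30 for F = 3, so variance rises by only 0.010/4 = 0.3% to 0.091/4 = 2.3%. Most of the loss therefore comes from the open lower end of the window.

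**Step 5: check the route to bias.** Section 4.4 says that outcome assessors, and the researcher collecting primary and secondary outcomes, are blinded to allocation. With 50 per arm, chance imbalance in timing has a standard error of added SD × √(2/50): 0.06 points for F = 1 and 0.17 for F = 3. The variance rise in step 2 already includes this. The 4 h shift would need a systematic difference in timing, and nothing in the documents provides for one.

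**The case against.** The strongest reply is that this is loose wording in a condensed article. The 24 h label in section 4.9 can be read as shorthand for the one postoperative visit, and the abstract places that visit on the next day. Section 4.7.3 says recovery-area data are collected in addition, which suggests an extra score and not a substitute. Visit tolerances and form fields usually sit in the full protocol, which is not shown. The effect size rests entirely on assumed figures, and at the low end it is negligible.

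Much of this stands. The timings are not all in conflict, the lack of a stated tolerance would not be a finding by itself, and the documents do not say how fast pain changes. But the shorthand reading does not settle which score is analysed. Even as an extra, the recovery-area score has no place in Table 2 or the mixed model, and it meets the stated limit for the postoperative row. These are conflicts in what the article states, not details it leaves out.

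A reader might also infer that the arms will be measured at different times, so that the pain comparison is biased. The documents do not support that. Only participants are incompletely blinded, and the recovery-area sentence, though it sits under the control-group heading, reads in context as applying to all patients.

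**Conclusion.** The point holds as a mismatch between the analysed pain endpoint and the collection schedule, with a recovery-area score left unassigned. The expected harm is extra variance and a mislabelled secondary outcome. Under the stated assumptions variance rises by about 2–19%, which is a loss of roughly 2–16% of effective sample. Even timing over 1–24 h is near a worst case, so if practice is in fact next-day the loss would be nearer the small figures in step 4. Bias of 0.17–0.52 points would follow only if mean collection times differed by 4 h between arms, which is a conditional risk and not a demonstrated one. The sample size and the primary comparison rest on STAI-S and are untouched. The change is worth making before collection because it is cheap and cannot be made afterwards.

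**What to change.** Reconcile the abstract, sections 4.5, 4.7.2, 4.7.3, 4.7.4 and 4.9, and Table 2 to one analysed postoperative VAS time:

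- State a narrow window, the same in all three arms. One example is a next-day assessment that stays inside the 24 h limit. A window reaching past 24 h would contradict that limit, and it might run into discharge given the 2-day expected stay in Table 1.
- Use the same label for that time point in section 4.9.
- Record the clock time of each score, so that time since surgery can be checked by arm.
- If a recovery-area score is kept, list it in Table 2 as a separately named time point and say that it never replaces the analysed score.

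The cost is wording in these places and one field on the form. The small downside is that assessments must be made in a set window. No extra patients are needed.
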